## Abstract

**Background:**

A septate uterus is a uterine anomaly that may affect reproductive outcome, and is associated with an increased risk for miscarriage, subfertility and preterm birth. Resection of the septum is subject of debate. There is no convincing evidence concerning its effectiveness and safety. This study aims to assess whether hysteroscopic septum resection improves reproductive outcome in women with a septate uterus.

**Methods/design:**

A multi-centre randomised controlled trial comparing hysteroscopic septum resection and expectant management in women with recurrent miscarriage or subfertility and diagnosed with a septate uterus. The primary outcome is live birth, defined as the birth of a living foetus beyond 24 weeks of gestational age. Secondary outcomes are ongoing pregnancy, clinical pregnancy, miscarriage and complications following hysteroscopic septum resection. The analysis will be performed according to the intention to treat principle. Kaplan-Meier curves will be constructed, estimating the cumulative probability of conception leading to live birth rate over time. Based on retrospective studies, we anticipate an improvement of the live birth rate from 35% without surgery to 70% with surgery. To demonstrate this difference, 68 women need to be randomised.

**Discussion:**

Hysteroscopic septum resection is worldwide considered as a standard procedure in women with a septate uterus. Solid evidence for this recommendation is lacking and data from randomised trials is urgently needed.

**Trial registration:**

Dutch trial registry (NTR1676, 18th of February 2009).

**Electronic supplementary material:**

The online version of this article (10.1186/s12905-018-0637-6) contains supplementary material, which is available to authorized users.

## Background

A septate uterus is a congenital uterine anomaly where the uterus is divided into two cavities. A septate uterus is associated with reduced fertility (RR 0.86; 95% CI 0.77–0.96), increased miscarriage rates (RR 2.9; 95% CI 2.0–4.1) and preterm delivery (RR 2.1; 95% CI 1.5–3.1) [1].

The mechanisms behind the negative effect of the septum on fertility and pregnancy outcome have not yet been clarified. Suggestions are that the septum is a poor site for embryonic implantation due to the assumed poor vascularization, decreased sensitivity to preovulatory changes of the endometrium overlying the septum, uncoordinated contractility of the septum, or a local defect of vascular endothelial growth factor (VEGF) receptors in the endometrium covering the septal area [2–5]. A septate uterus is usually ascertained through recurrent pregnancy loss or subfertility, and occasionally by other complaints such as dysmenorrhoea or preterm birth. Approximately 6% of women with recurrent miscarriage and 3.5–6.4% of subfertile women, has a septate uterus [6–8]. .In comparison, this prevalence is 2–3% in the general female population [6, 7].

Although evidence for the effectiveness of resecting the uterine septum is limited, resection is considered standard care in many countries. The evidence is mainly based upon retrospective studies, in which improved pregnancy chances and live birth rates after hysteroscopic septum resection have been suggested [9–17].

The major flaw in most of the abovementioned studies is obviously the before/after design, since this will always favour the tested intervention as the prognosis without the intervention is usually good [18, 19]. At this moment, in view of the limited quality of the performed studies it thus remains unclear whether removal of the septum will eliminate negative effects –if any- of a septate uterus, and whether the procedure does not cause harmful side effects [20] .

To assess whether surgical intervention in women with (recurrent) miscarriage, subfertility or preterm birth and a septate uterus will improve reproductive outcome, we propose The Randomised Uterine Septum Trial (TRUST).

## Methods

### Design

The Randomised Uterine Septum Trial (TRUST) is a multicentre randomised controlled trial in women with a septate uterus (NTR 1676). Women are randomised to hysteroscopic septum resection or expectant management. Recruitment has started since October 2009 and is ongoing.

### Trial population

The study population consists of women of reproductive age with a septate uterus and a history of (recurrent) miscarriage, subfertility or preterm birth (Fig. 1). Women with a contraindication to surgery are excluded for the trial. When the study started in 2008, the study population consisted of women with recurrent miscarriage and a septate uterus. During the course of the trial we found out that it was difficult to recruit and randomize women for the study. Since essentially the population is women with a septate uterus and a wish to conceive, we decided to broaden the inclusion criteria to make an effort to identify these women more easily. Thus in 2011 we extended the inclusion criteria into women with a septate uterus and recurrent miscarriage and/or subfertility, and in 2015 the inclusion criteria were extended to women with (recurrent) miscarriage, subfertility or preterm birth. All amendments were approved by the ethical committee of the Academic Medical Centre (AMC), Amsterdam. Recurrent miscarriage is defined as two or more, not necessarily consecutive, pregnancy losses before 20 weeks of gestational age. Subfertility is defined as the inability to conceive for a minimal period of one year of trying to conceive. The definition of preterm birth is birth before a gestational age of 37 complete weeks. Only women with an active wish to conceive are eligible for the trial. Following the most recent ESHRE-ESGE classification, a septate uterus is defined as all cases with an abnormal resorption of the midline septum, a normal outline of the uterus and an internal indentation at the fundal midline exceeding 50% of the uterine wall thickness regardless of the size of the septum [21]. Over the years there has been a lot of discussion about the classification system of uterine anomalies and ideas about the best definition of the septate uterus have changed [22]. After the following publication of the ESHRE-ESGE classification, we have adjusted the definition in the study protocol accordingly to these new insights, but it did not change our patient population [21].The presence of a uterine septum is ascertained by HSG, 3D ultrasound (3D-US), MRI, saline or gel infusion sonohysterography or hysteroscopy combined with laparoscopy [23–26].

**Fig. 1 Fig1:**
[figure not shown]
Flowchart

### Recruitment procedure

Women are recruited from outpatient clinics located in the Netherlands, Iran and the United States of America. Women are invited to take part in the study when a septate uterus is diagnosed and when they meet the inclusion criteria.

### Ethics and trial registration

Approval for this study and all subsequent amendments have been obtained from the Medical Ethical Committee of the Academic Medical Centre (IDS NL24082.018.08 MEC Academic Medical Centre, Amsterdam) The Netherlands. Local approval is obtained at all participating centres or will be obtained before the start of recruitment. The trial is registered within the Dutch trial registry (NTR1676).

Written informed consent is obtained from women fulfilling the inclusion criteria, prior to randomization.

### Randomization

Once eligibility for the trial has been confirmed and women have given informed consent they are randomised via a web-based central randomization system to receive either hysteroscopic septum resection or expectant management .

### Hysteroscopic septum resection

The intervention is hysteroscopic septum resection. The choice for an instrument and distension medium may vary per hospital and depends on the preference of the surgeon and instruments available. Analgesia during surgery can be either general anaesthesia or a loco-regional technique depending on the preference of the woman and whether concomitant surgery, in the form of laparoscopy, is scheduled. To prevent uterine perforation during surgery, a laparoscopy or ultrasound has to be performed simultaneously [27]. The choice for laparoscopy or ultrasound depends on the local hospital protocol. To assess the results of the resection, a diagnostic hysteroscopy is performed 6–8 weeks postoperatively in an outpatient setting. When a secondary surgery is needed, this will be specified.

### Expectant management

The control group will receive expectant management. Additional interventions, such as for example aspirin or heparin in case of co-existing antiphospholipid syndrome, or additional artificial reproductive techniques in women with subfertility, are allowed in both groups and will be registered. Should the first pregnancy after randomization result in a miscarriage, or should pregnancy not occur after one year of follow-up, women are free to opt for additional therapy, including hysteroscopic septum resection.

### Outcome measures

The primary outcome measure is live birth, defined as the birth of a living foetus beyond 24 weeks of gestational age.

Secondary outcomes are ongoing pregnancy, clinical pregnancy, miscarriage, pregnancy outcomes as placental abruption, uterine rupture, preterm birth and mode of delivery (vaginal versus caesarean section), perinatal morbidity, mortality and complications following hysteroscopic septum resection, such as uterine perforation, fluid overload and endometritis.

### Follow up

Follow up will take place for at least one year. Women who will conceive in that period will be followed for the course of that pregnancy. Woman allocated for expectant management, have the opportunity to opt for a hysteroscopic septum resection after one year of follow up, or when the next pregnancy results in a miscarriage. An additional timeline shows more detail on the timeline of study (see Additional file 1).

### Statistical analysis

All analyses will be performed according to an intention to treat basis. The primary outcome, live birth, will be compared between the intervention and control group.

Relative risks and 95% confidence intervals will be calculated for the relevant outcome measures. Time to conception, resulting in live birth will also be assessed by means of life table analysis. To estimate the cumulative probability of conception resulting in live birth rate over time Kaplan-Meier curves will be constructed. The risk of premature birth will be estimated stratified for gestational age. The relative risk for obstetrical and surgical complications will be calculated.

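### The planned relative risk for surgical complications does not estimate the risk of the resection, because the control arm has no allocated surgery

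*Protocol article*

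**What the plan says.** Four sections of the protocol article bear on this.

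- **Statistical analysis:** "All analyses will be performed according to an intention to treat basis", with no exception for safety. Later in the same section: "The relative risk for obstetrical and surgical complications will be calculated". The only groups the section names are intervention and control.
- **Outcome measures:** the surgical safety outcome is given as "complications following hysteroscopic septum resection, such as uterine perforation, fluid overload and endometritis".
- **Expectant management:** "The control group will receive expectant management". After a miscarriage in the first pregnancy, or a year without pregnancy, "women are free to opt for additional therapy, including hysteroscopic septum resection".
- **Follow up:** "Follow up will take place for at least one year", extended through any pregnancy conceived in that period. Women in the expectant arm "have the opportunity to opt for a hysteroscopic septum resection after one year of follow up, or when the next pregnancy results in a miscarriage".

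The article gives no expected complication rate and no expected crossover share. It does not say how a complication of a control woman's resection is to be attributed.

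**The concern.** A relative risk compares the risk of the same event in two groups that can both have it. Here the event is defined by having had a resection, and one group is not allocated to resection. The control count is therefore zero by construction unless controls are operated on. When they are, the intention-to-treat rule attributes the complication to expectant management.

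The Background says it is unclear whether the procedure has harmful side effects, and the Abstract says convincing evidence on its safety is lacking. The quantity that answers this is the risk among women who have the operation. The stated statistic does not estimate it, whether or not controls cross over.

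**Working it through.** **Inputs from the article.** 35% against 70% live birth, two-sided 5%, 80% power, two groups of 31, plus 10%, giving 68 randomised (Sample size).

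**Assumptions.** The article gives no complication counts, per-operation risks or crossover shares, so those below are illustrative.

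**1. Group size.** With pooled variance and no continuity correction, the mean proportion is 0.525 and

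n = [1.96·√(2·0.525·0.475) + 0.8416·√(0.35·0.65 + 0.70·0.30)]² / 0.35²
= (1.384 + 0.557)² / 0.1225 ≈ 30.8, so 31 per arm.

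Then 62 × 1.1 = 68.2, stated as 68, or 34 per arm. The plan's figure reproduces. It is used below only as a group size.

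**2. No control woman has an event.** RR = (a/34)/(0/34). This is 0/0 if a = 0 and infinite if a ≥ 1. Adding 0.5 to each cell gives a finite number. The plan does not mention this correction; it is tried here only to see whether it rescues the ratio. For 2 against 0:

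- RR = 2.5/0.5 = 5.0
- SE of log RR = √(1/2.5 − 1/35 + 1/0.5 − 1/35) = 1.531
- 95% CI = 5.0 × exp(±1.96 × 1.531) = 0.25 to 100

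For 1 against 0 the result is 3.0 (0.13 to 71), and for 3 against 0 it is 7.0 (0.38 to 131). None of these intervals is informative.

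**3. Some control women have a resection during follow-up.** Let r be the risk per operated woman, equal in both arms, let x be the share of controls operated on, and let every woman allocated to surgery have it. The ratio of expected risks is r/(x·r) = 1/x, and r cancels.

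| Assumed crossover share x | Ratio 1/x |
|---|---|
| 10% | 10 |
| 20% | 5 |
| 30% | 3.3 |
| 50% | 2 |

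One crossover event changes 2 against 0 into 2 against 1: RR = 2.0, SE = √(1/2 − 1/34 + 1 − 1/34) = 1.20, 95% CI 0.19 to 21.

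Even with crossover, the control count will often still be zero. The chance of no control event is (1 − r·x)^34. At x = 20% this is 87% for r = 2% and 50% for r = 10%.

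**4. Risk among operated women.** Exact (Clopper-Pearson) 95% intervals, with 34 operated women assumed:

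| Women with an event | Proportion | Exact 95% CI |
|---|---|---|
| 0 of 34 | 0% | 0 to 10.3% |
| 1 of 34 | 2.9% | 0.07% to 15.3% |
| 2 of 34 | 5.9% | 0.7% to 19.7% |
| 3 of 34 | 8.8% | 1.9% to 23.7% |

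The upper limit for 0 of 34 is 1 − 0.025^(1/34) = 10.3%. If only 31 women are operated on, the results are close: 0 events give an upper limit of 11.2%, and 2 events give 6.5% (0.8% to 21.4%).

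**The case against.** The strongest reply is that this is one word of wording on a late-listed secondary outcome. A condensed article may leave the safety set and the interval method to a fuller document, and the counts would be available whatever ratio is attempted. The low rank is accepted. The reply does not remove the point, because the article does not leave the measure open: it names a relative risk for surgical complications and a blanket intention-to-treat rule. An analysis plan that follows those words inherits the problem, and one that departs from them contradicts the article.

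Other objections limit the point and stand in part.

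- **The comparison is not spelled out.** That the ratio is between arms is an inference, but a relative risk needs two groups and no others are named.
- **Endometritis or perforation could in principle arise without a resection.** True. The structural zero rests on reading surgical complications in the analysis section as the outcome defined under Outcome measures, which is the natural reading.
- **Many crossovers may fall outside observation.** Follow-up is guaranteed for one year plus any pregnancy conceived in it. A resection chosen after one year may count in neither arm. One that follows an early miscarriage can fall within the year.
- **The event counts are invented.** They are illustrations, and the structural argument does not depend on them.

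A reader might infer that the plan would conceal harm, with a wide interval presented as no significant increase. The article does not support that. It mentions no continuity correction, no significance test for complications and no withholding of counts.

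**Conclusion.** The stated statistic fails for complications of resection. With no control-arm event it is undefined or infinite. With crossover events inside follow-up it tends to 1/x, a measure of crossover and not of the operation. This rests on two readings: that the relative risk compares the randomised arms, and that surgical complications are the events defined as following resection. The 1/x result also assumes equal risk per operated woman in both arms and that all women allocated to surgery have it.

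A reader might go further and conclude that every crossover complication will count against expectant management. That holds only for resections within the observed follow-up.

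The point is minor. It touches a secondary safety outcome. The relative risk for obstetrical complications is meaningful, and the live birth analysis and sample size are unaffected.

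**What to change.** Replace the sentence on complications with wording along these lines:

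*Complications of septum resection will be reported as the number and proportion of women with at least one complication, among all women who had a resection during follow-up, with exact 95% confidence intervals. Women randomised to resection and women who crossed over will be shown separately, and repeat resections will be listed separately. No relative risk will be calculated for these complications. For obstetrical complications, relative risks between the randomised groups will be calculated by intention to treat.*

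The woman is the unit because repeat operations in one woman are not independent, and an exact binomial interval needs independent units. If no complication occurs, the upper confidence limit should still be stated.

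The cost is one short passage in the analysis section and one table, with no extra participants. The complications are already listed outcomes, and the Hysteroscopic septum resection section says secondary surgery will be specified. The article does not say that complications of control-arm resections are collected, least of all for operations after the guaranteed follow-up. The set is therefore limited to resections during follow-up, and the data collection should be checked for these women.

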### Sample size

The sample size is based on retrospective studies, anticipating an improvement of the live birth rate from 35% without surgery to 70% with surgery. Using a two-sided test, an alpha-error of 5% and a beta-error of 20%, two groups of 31 women are needed to demonstrate this difference. Anticipating lost-to-follow up and protocol violation, an additional 10% is needed. Thus, 68 women need to be randomised.

## Discussion

Until this date, hysteroscopic septum resection of a septate uterus is standardly being performed worldwide in women of reproductive age and a wish to conceive [28, 29].

The evidence for this recommendation is based on retrospective and prospective comparative studies that suggest that restoration of the uterine morphology can potentially have a positive effect on live birth rate [9–17]. Most retrospective studies used their own participants as a control group. To our knowledge, over the years nine prospective comparative studies have been published. The studies describe miscarriage, pregnancy or live birth rate in women with a septate uterus who consented to hysteroscopic septum resection, compared with women who chose expectant management. These studies published contradictory findings, with some studies showing significant higher pregnancy rate in women with a septate uterus who were treated with surgery [12, 13, 30, 31], while other studies found no significant difference [32–35]. Thus, equipoise still exists and data from randomised trials are needed to provide definitive proof of effectiveness of a septum resection, or the lack thereof. In view of the major improvements in pregnancy rates reported by the non-comparative retrospective studies, we require a low number of participants to exclude a difference of 35% or more. By broadening our inclusion criteria we did not need to re-calculate the sample size since our primary population, i.e. women of reproductive age with a septate uterus, remained the same. Over the years, many studies have been published about the classification of uterine anomalies and the interrater disagreement in diagnosing the septate uterus still exists [36, 37]. We have changed the definition of the septate uterus according to new insights leading to the ESHRE ESGE classification, and in retrospect all women meet these new criteria [21].

To our knowledge the TRUST trial is the first registered multi centre randomised controlled trial designed to assess whether hysteroscopic septum resection improves live birth rate (NTR1676). If hysteroscopic septum resection proves to be without effect on reproductive outcome, this would imply a major change in treatment policy and adapted guidelines.

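### The Discussion lets a null result count as lack of effect, but the design can at best exclude a gain of about 35 points

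*Protocol article*

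**What the plan says.** The Sample size section describes a superiority comparison: "The sample size is based on retrospective studies", "anticipating an improvement of the live birth rate from 35% without surgery to 70% with surgery". The error rates are given as "Using a two-sided test, an alpha-error of 5% and a beta-error of 20" per cent. This yields 31 women per arm and, with 10% added, 68 randomised.

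The Discussion then makes three statements about what the trial can deliver:

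- Randomised data are needed to "provide definitive proof of effectiveness of a septum resection, or the lack thereof".
- On size, "we require a low number of participants to exclude a difference of 35% or more".
- On consequences, "If hysteroscopic septum resection proves to be without effect on reproductive outcome, this would imply a major change in treatment policy".

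For the estimate, the Statistical analysis section says "Relative risks and 95% confidence intervals will be calculated for the relevant outcome measures". It adds life-table and Kaplan-Meier analyses of conception leading to live birth.

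The Background criticises the before/after design of most earlier studies, "since this will always favour the tested intervention as the prognosis without the intervention is usually good".

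**The concern.** The three Discussion statements do not fit together. Excluding a gain of 35 points or more is a limited and roughly attainable aim. Showing that an operation lacks effect is a much larger claim, because it requires ruling out every gain that would matter to patients. The article names no such smaller gain and ties the larger claim to a change of guidelines.

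The article's own reasoning makes the gap matter. The 35-point effect comes from retrospective studies. The Discussion says that most of these used their own participants as controls, and the Background says that such designs favour the intervention. True effects below 35 points are therefore to be expected, and for those the trial has little power. If a gain of 15 or 20 points exists, a non-significant result is the more likely outcome. Under the article's wording, that result could be taken as grounds for abandoning the operation.

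**Working it through.** **Inputs (Sample size section).** Live birth 35% versus 70%; two-sided alpha 5%; power 80%; 31 per arm evaluable; 68 randomised, so 34 per arm if nobody is lost.

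**1. The plan's own figure.** Pooled-variance formula, no continuity correction, mean rate 0.525:

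n = [1.96·√(2·0.525·0.475) + 0.842·√(0.35·0.65 + 0.70·0.30)]² / 0.35² = (1.384 + 0.557)² / 0.1225 = 30.8, so 31 per arm.

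Adding 10%: 62 × 1.10 = 68.2, stated as 68. The sample size reproduces. Power for 35% versus 70% is 80% at 31 per arm and 84% at 34.

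**2. Can the design exclude 35 points?** The upper 95% (Wald) limit of the risk difference must fall below 0.35 when the true difference is zero. By exact binomial enumeration, for a common rate of 35% or 50%:

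| Common rate | 31 per arm | 34 per arm |
|---|---|---|
| 35% | 83% | 87% |
| 50% | 81% | 82% |

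The one quantified claim in the Discussion is therefore roughly met.

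**3. What does a flat result leave open?** With equal observed rates p, the half-width is 1.96·√(2p(1−p)/n):

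| Observed rate in both arms | 31 per arm | 34 per arm |
|---|---|---|
| 35% | 23.7 points | 22.7 points |
| 50% | 24.9 points | 23.8 points |

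The Newcombe interval gives 22.7 points for 11/31 in each arm and 21.7 for 12/34 in each arm, so the result does not depend on the Wald approximation.

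On the relative-risk scale, 11/31 versus 11/31 gives a standard error of log RR of √(2·(1/11 − 1/31)) = 0.342. The interval is exp(±1.96 × 0.342) = 0.51 to 1.96. A near-doubling of live birth remains compatible with identical observed rates.

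**4. Power for smaller true gains over 35%.** Power = Φ[(d − 1.96·s₀)/s₁], where s₀ is the pooled and s₁ the unpooled standard error. For d = 0.20 and n = 31, s₀ = 0.1264 and s₁ = 0.1238, so power = Φ[(0.20 − 0.2477)/0.1238] = 35%.

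| True gain | 31 per arm | 34 per arm |
|---|---|---|
| 15 points | 22% | 24% |
| 20 points | 35% | 38% |
| 25 points | 51% (50.5%) | 54% |
| 35 points | 80% | 84% |

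Gains of 15 to 20 points would thus be missed in about 62–78% of trials.

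**5. What excluding smaller gains would take.** With no true difference, 35% in both arms, one-sided 2.5% and 80% power, n = (1.96 + 0.842)²·2·0.35·0.65 / m². This gives about 90 per arm for a margin m of 20 points, 159 for 15 and 358 for 10. These margins are illustrative; the article gives none.

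**The case against.** The best defence is that the article never says a non-significant test will be read as no effect. The closing sentence is conditional, the sentence about definitive proof speaks of randomised trials in general, and the analysis section commits to confidence intervals. All of that is true. A reader might infer a stated intention to equate non-significance with no effect, and the text does not go that far. What stands is that the article offers proof of lack of effect as an attainable result, attaches a policy consequence to it, and in the same section describes a size that serves only to exclude 35 points.

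Other stronger readings are also unsupported:

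- *The sample size is wrong.* It is not; it reproduces exactly, and the 35-point exclusion is roughly achieved.
- *The trial can never exclude gains below about 24 points.* That limit holds for a zero observed difference and observed rates near 35–50%. If surgery looked worse, smaller gains could be excluded. With no true difference, the upper limit falls below 20 points in about 35–42% of trials (exact binomial, common rate 35–50%). If surgery looked slightly better, the limit would be higher.
- *Only a relative measure is planned.* The Kaplan-Meier curves give absolute cumulative probabilities by arm. They do not, however, give a risk difference with an interval for the primary outcome.
- *Later septum resection in control women drives the trial to a null result.* The article allows it after one year or after a miscarriage, but whether later births count is not stated there and the timeline file is not shown. Its size cannot be judged.

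A last objection is that a rule for interpreting results belongs in an analysis plan that is not shown. The absence of such a rule is not the point here. The point is a printed claim that conflicts with the printed sample size, and no analysis plan can make 31–34 women per arm show lack of effect.

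**Conclusion.** Wrong as written, of moderate severity. The sample size and the 35-point exclusion claim stand; the wording on lack of effect does not. Equal observed rates of 35–50% would still leave a gain of about 23–25 points open, and power for true gains of 15, 20 and 25 points is about 22–24%, 35–38% and 51–54%.

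These figures assume 31–34 analysed women per arm, the article's 35% control rate for power, a two-sided 5% level and no dilution from later surgery in the control arm. That smaller effects are plausible follows from the article's own criticism of the earlier studies; no outside estimate is used. No planned analysis is shown to be invalid.

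**What to change.** 1. In the Discussion, replace the wording on lack of effectiveness and on resection being without effect. Say that a non-significant result excludes only gains above the upper 95% confidence limit and is otherwise inconclusive.
2. In the Statistical analysis section, report the live-birth risk difference with its 95% confidence interval beside the relative risk, because the design target is an absolute difference.
3. In the Sample size section, state that 80% power applies to a 35-point gain only.

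A per-protocol analysis that counts control women only until they have a resection should not be added as a remedy. It would stop follow-up after miscarriage or failure to conceive, in one arm only. That is outcome-dependent and tends to favour surgery.

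The cost is wording and one extra estimate, with no additional participants. The price is that the stated reach of a null result becomes less favourable. The article describes recruitment as ongoing, so on its account the change can be made before results are known.
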